**Table 9. End-of-Treatment Visits Process**

| **End of Treatment** | **±3 days** | **Note**  **21 days (±7 days)** |
| --- | --- | --- |
| Vital Signs | X | Vital signs include: temperature, pulse rate, respiratory rate, and blood pressure.  Refer to section 13.1.2 |
| Weight | X | Refer to section 13.1.2 |
| Physical Examination | X | Refer to Program 13.1.2 |
| ECOG PS Sore | X | Refer to section 13.1.2 |
| Laboratory Tests | | |
| 12-lead ECG | X | Refer to section 13.1.2 |
| Hematology/Blood Biochemistry/Urine /Stool Test | X | Refer to section 13.1.1 |
| Coagulation | X | Refer to section 13.1.1 |
| Pregnancy Test | X | Refer to section 13.1.2 |
| Thyroid Function | X | Refer to section 13.1.2 |
| Myocardial Enzyme Test | X | Refer to section 13.1.2 |
| Pituitary-adrenal axis Test | X | For hospitals where conditions permit. |
| Echocardiography | X | Refer to section 13.1.2 |
| Pulmonary Function Tests and Arterial Blood Gases |  | When clinically indicated in the judgment of the investigator. |
| AE Assessment | X | The safety assessments for AEs and laboratory tests will be performed according to NCI CTCAE v5.0. All AEs that occur after signing the informed consent form to 30 days after the last dose must be monitored and documented. If a subject starts a new anti-tumor treatment during the AE collection period, then only treatment-related AEs should be collected after the start of new anti-tumor treatment. |
| Concomitant Medications | X | All concomitant medications/treatments from 28 days prior to study treatment until the end of the safety follow-up period should be collected. If a subject starts a new systemic anti-tumor treatment during the study, then only concomitant medications/treatments used for study treatment-related AEs should be documented. |
| Evaluation of efficacy | | |
| Imaging Evaluation | X | Refer to section12.3 and 12.4 |
| Biomarker Exploration | | |
| Archived or Fresh Tumor Tissue Specimens | X | At least 10 white sheets 4-6 μm thick (optional) |
| Peripheral Blood Test | X | 16 mL of peripheral blood was taken for tumor marker testing. |

## Safety Follow-Up

Safety follow-up will be conducted 90±7 days after the last dose. Refer to Table 10 for safety follow-up process.

**Table 10. Safety Follow-up Process**

| **Safety Follow-Up** | **42±7 days** | **Note** |
| --- | --- | --- |
| Vital Signs | X | Vital signs include: temperature, pulse rate, respiratory rate and blood pressure.  Refer to 13.1.2 |
| Weight | X | Refer to 13.1.2 |
| Physical Examination | X | Refer to section 13.1.2 |
| ECOG PS Score | X | Refer to section 13.1.2 |
| Laboratory Tests | | |
| 12-lead ECG | X | Refer to section 13.1.2 |
| Hematology/Blood Biochemistry/Urine /Stool Test | X | Refer to section 13.1.1 |
| Coagulation Function | X | Refer to section 13.1.1 |
| Thyroid Function Test | X | Refer to section 13.1.2 |
| AE Assessment | X | All AEs that occur after signing the informed consent form to 30 days after the last dose must be monitored and documented. If a subject starts a new anti-tumor treatment during the AE collection period, then only treatment-related AEs should be collected after the start of new anti-tumor treatment. |
| Concomitant Medications | X | All concomitant medications/treatments from 28 days prior to study treatment until the end of the safety follow-up period should be collected. If a subject starts a new systemic anti-tumor treatment during the study, then only concomitant medications/treatments used for study treatment-related AEs should be documented. |
| End-of-Treatment Visits | | |
| State of Survival | X | Once every 3 months after finished treatment. |
| Follow-up Anti-Tumor Therapy | X |  |
| Evaluation of Efficacy | | |
| Imaging Evaluation | X | For discontinuation of therapy for reasons other than imaging PD, imaging evaluations will be performed according to the imaging evaluation time cutoffs, to the extent possible, until either of the following events occurs: initiation of a new antitumor therapy, PD, subject withdrawal of ICF, and death. |

# CLINICAL EVALUATION

## Primary Efficacy Indicators

- Safety : Evaluated according to CTCAE 5.0 criteria.

## Secondary Efficacy Indicators

- Progression-free survival (PFS)：PFS was determined as the interval from initiation of the study dose to disease progression or death, whichever occurred first.
- Overall survival (OS): OS was determined as the interval from initiation of the study dose to death from any cause.
- Overall survival (ORR): ORR was determined as the percentage of patients who had complete response (CR) or partial response (PR) as best overall response per RECIST v1.1.
- Disease control rate (DCR): DCR was defined as the percentage of patients with CR, PR or SD. DoR was determined as the interval from the initial documented objective response to disease progression or death from any cause.

## Imaging Scan Site

The method used for tumor imaging evaluation at baseline must be consistent with the method used for each subsequent follow-up evaluation, and a computed tomography (CT) or magnetic resonance imaging (MRI) scan is recommended. Other sites of involvement are examined as prompted by each subject's symptoms and signs. Thoracic, abdominopelvic (scans from the apex of the lungs to the suprapubic symphysis), brain, and bone scans, as well as all known or suspected sites of disease, must be performed at baseline. Each subsequent clinical tumor imaging evaluation should include thoracic abdominal and pelvic, and may include brain and/or bone scans when clinically indicated. Investigators may increase the frequency of imaging surveillance as appropriate.

## Evaluation Time Point

Baseline tumors will be performed within 28 days prior to the first dose, and imaging obtained prior to signing informed consent may be used for screening phase tumor assessment as long as it meets protocol requirements. Imaging evaluations of C1D21 and C1D21 were performed every 6 weeks (±7 days) thereafter until imaging PD was recorded.

If the investigator is unable to determine whether the disease has progressed, especially if there is uncertainty about the certainty of non-target lesions and new lesions, the subject may continue treatment and the subject's disease status may be reassessed when clinical indication occurs, or at the next scheduled evaluation time point. The date of progression should be the date of initial detection if PD is confirmed on scan review.

Suspension of one or more study drugs does not affect the frequency of RECIST v1.1 assessments.

# SECURITY ASSESSMENT

## Security Indicators

### Indicators for routine laboratory safety assessment

**Table 11. Routine Laboratory Safety Assessment**

| Hematology Test | RBC, HGB, HCT, WBC, PLT, LYM, ANC, MONO, EOS and BASO |
| --- | --- |
| Coagulation Function | TT, PT, APTT and INR |
| Blood Biochemistry | TBIL^a^, ALT, AST, γ-GT , ALP, ALB, TP, LDH, BUN, Cr, Na, K,  Cl, Mg, Ca, P, lipase, amylase, and FBG |
| Urine Routine | PH, UALB, UPRO^b^, URBC^c^ and UGLU |
| Stool Test | occult blood (in medicine, fecal blood from internal bleeding) |

1. If TBIL ≥ 2 × ULN (and there is no evidence of Gilbert's syndrome), then direct and indirect bilirubin were measured separately.
2. Leukocytes should be examined microscopically (if appropriate) and erythrocytes should be examined with a high magnification field of view.

### Physical examination

A complete physical examination includes: general condition, respiratory, cardiovascular, abdominal, skin, head and neck (including ears, eyes, nose, and throat), lymph nodes, thyroid, musculoskeletal (including spine and extremities), genital/anal, and neurologic evaluation.

1. **12-lead electrocardiogram**

Resting 12-lead ECGs will be analyzed at a local laboratory according to the visit schedule. A 12-lead ECG should be performed in each case after the subject has rested in the prone position for at least 5 minutes, and further ECGs will be performed when clinically indicated cardiac-related event. The investigator completes the ECG assessment on the day of the examination and records the results on the ECG. The same assessment should be used throughout the study.

ECGs will be recorded at 25 mm/sec. The investigator should evaluate all ECGs according to the category of clinically significant abnormality/non-clinically significant abnormality; if there is a clinically significant abnormality results, the investigator should document the result as an AE in the CRF.

1. **Vital signs**

Vital signs will be checked as described in the study visit schedule. Vital signs include temperature, pulse rate, respiratory rate and blood pressure.

Additional vital sign assessment monitoring may be performed at the discretion of the investigator in accordance with standard clinical practice or based on clinical need.

In the presence of AE/SAE, additional recorded vital sign values may be taken on the CRF (if applicable).Record the date and time of collection and measurement in the appropriate section.

- 1. **Pulse and blood pressure**

Pulse and blood pressure were taken during the Screening Period and prior to the planned administration of the daily infusion of Camrelizumab.

Blood pressure monitoring: For each blood pressure measurement, no smoking or coffee for 30 minutes prior to the measurement and rest quietly for at least 10 minutes.

Minutes were taken in a sitting position with the elbow placed at the same level as the heart, and each blood pressure measurement was taken on the same side.

Blood pressure was measured by the investigator during the screening period and prior to each scheduled administration of camrelizumab; during the study, blood pressure monitoring was done by the subjects themselves and recorded on subject diary cards, and blood pressure was measured weekly for the first 2 cycles.

- 1. **Body temperature and breathing**

Temperature and respiration were taken during the screening period and prior to the planned administration of the daily infusion of camrelizumab.

- 1. **Height and weight**

Height measurements were taken only during the Screening Period, and weight measurements were required during the Screening Period, prior to the administration of camrelizumab at each visit, at the end of treatment, and at the safety follow-up visit.

- 1. **Pregnancy test**

Women of childbearing potential undergo a serum human chorionic gonadotropin (hCG) sample pregnancy test within 7 days prior to the first dose of study drug. If the result is positive, the subject is ineligible for enrollment and must discontinue participation in the study. Pregnancy suspected to have occurred during the study should be reviewed.

- 1. **Other tests**
- Hepatitis B tests: HBsAg, HBsAb, HBcAb, HBeAg, HBeAb.
- HIV antibody, HCV antibody tests.
- Thyroid function tests: T3, T4, TSH, FT3, and FT4.
- Myocardial enzyme profile tests: LDH, AST, CK, CK-MB and ALT.
- Echocardiography.
- Lung function tests: VT, BE, MV, ERV, IC, VCmax, FVC, FEV1, FEV1/FVC, PEF, MEF75, MEF50, MEF25, MVV, TLC, RV/TLC, BR, DLCO SB, Raw, eff and sGaw eff.
- Arterial blood gas analysis: including Ph, PaCO2, AB, SB, BB, BE, TCO2, CO2-CP, PaO2, and SaO2 metrics were assessed.

## Adverse Event

Adverse Event (AE) Definition: an AE is any unfavorable medical event that occurs after a subject or clinical trial participant receives a drug or treatment regimen that is not necessarily causally related to the treatment.

AE can be any sign (including abnormal laboratory test results), symptom, or disease that is unpleasant or unrelated to the purpose for which the product was used, whether or not it is considered to be related to the medical product, that is temporally related to the use of the medical product.

Events that occur during the pre- and post-treatment phases are also considered AEs under the regulations. Therefore, safety monitoring of AE or reporting of SAEs should begin once the subject participants in(signs the informed consent form) and continue through the end-of-trial visit.

## AE Classification

AEs are categorized as grades 0-5 according to the NCI-CTCAE 5.0. Classification Criteria. If the NCI AEs not listed in the toxicity grading criteria may be judged according to the following criteria:

- Grade 1: Mild, no clinical symptoms or cyanotic clinical symptoms; only clinical or laboratory test abnormalities; no treatment required; does not affect normal daily activities;
- Grade 2: Moderate, requiring minimal, localized or non-invasive treatment; interferes with normal daily activities (cooking, shopping, talking on the phone, counting money, etc.)
- Class 3: Serious or medically serious symptoms that are not life-threatening for the time being; result in hospitalization or prolonged hospitalization; result in disability; inability to work or perform normal daily activities (bathing, dressing, undressing, eating, going to the bathroom, taking medication, etc.), non-bedridden;
- Grade 4: life-threatening, requiring urgent treatment;
- Grade 5: death due to adverse event.

## AE Records

The name, severity, time of presentation, duration, management measures, and regression of various AEs occurring during the trial were recorded in detail and faithfully filled in the case report form (CRF). Abnormal laboratory test data should be recorded in the CRF. The test was repeated at least once a week until normalization or the end of the study. 30 days after the last dose of

Adverse events that occur within days are reported and recorded.

## AE Causality Assessment with Investigational Medicinal Product

Possible associations between AEs and the test drug were assessed according to a five-level classification of "definitely related, highly likely related, possibly related, possibly unrelated, and unrelated" (see Table 12.)

The levels of “definitely related, highly likely related, possibly related” were considered drug-related. The following table shows the criteria for determining the relationship between AE and drug:

**Table 12. Criteria for Determining the Relationship between AE and Medications**

|  | Definitely Related | Highly likely Related. | Possibly Related | Possibly Unrelevant | Unrelated |
| --- | --- | --- | --- | --- | --- |
| Reasonable chronology | √ | √ | √ | √ | × |
| Types of reactions to known drugs | √ | √ | √ | × | × |
| Removing the cause can improve | √ | √ | √ or × | √ or× | × |
| Re-administration can be repeated | √ | ? | ? | ? | × |
| There may be another explanation for the reaction | × | × | × | √ | √ |

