# STUDY ENPOINTS

## Primary Endpoints

- Safety (per CTCAE 5.0 criteria)

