## Statistical analysis plan

The results of this trial were mainly described statistically. Continuous data are presented with mean, standard deviation, median, maximum, and minimum values, while count data and ordinal data are presented with frequency (percentage), rate, and confidence interval. All statistical analyses will be programmed and calculated using SAS 9.3 statistical analysis software OR R version 3.4.1. All statistical tests will be two-sided, with a p-value less than or equal to 0.05 being considered statistically significant, and 95% confidence intervals will be used for the differences tested.

Basic patient characteristics are presented with mean, standard deviation, median, maximum and minimum values for quantitative data, and frequencies and percentages were listed for qualitative data.

Efficacy analysis: median PFS and its 95% CI were calculated using the kaplan-Meier method and their survival graphs were plotted for comparison. For secondary efficacy indicators, the kaplan-Meier method was used to estimate the median OS and its 95% CI, and survival graphs were plotted. Objective remission rate (ORR=CR+PR) and disease control rate (DCR=CR+PR+SD) were calculated and their 95% CIs. Quality of life scores were compared with baseline values using paired t-tests or signed rank-sum tests to compare the before-and-after differences within groups.

Safety evaluation: descriptive statistical analysis is the main focus, the table describes the adverse events and adverse reactions that occurred in this trial. (where an adverse reaction is defined as “an adverse event that is 'definitely related/highly likely related/possibly related' to the study drug”) Laboratory test results describing pre-test normal but post-treatment abnormalities and the relationship to the test drug when abnormal changes occurred.

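### Table 12 sets the bar for *possibly related* too high and leaves common causality patterns without a category, so the adverse-reaction rates may be understated or depend on the assessor

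*Protocol*

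**What the plan says.** Protocol section 13.5 uses five causality levels and then reduces them to two: "The levels of “definitely related, highly likely related, possibly related” were considered drug-related". Table 12 defines each level by five questions. Two rows matter here:

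- "Types of reactions to known drugs" is √ for definitely, highly likely and possibly related, and × for possibly unrelated and unrelated.
- "There may be another explanation for the reaction" is × for the three related levels, and √ for the two unrelated ones.

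Section 14.4 carries the result into the analysis. It defines an adverse reaction as "an adverse event that is 'definitely related/highly likely related/possibly related' to the study drug".

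The protocol also has all-cause provisions. Safety by CTCAE 5.0 is the primary endpoint (section 2.1) and is not limited to related events. Section 13.2 defines an adverse event "whether or not it is considered to be related to the medical product". Tables 7 to 10 require all adverse events to be documented from consent to 30 days after the last dose. In section 14.4, "the table describes the adverse events and adverse reactions that occurred in this trial".

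Causality controls data capture in two places. Once a new anti-tumor treatment starts, Tables 7 to 10 limit collection to treatment-related events. Section 13.7 says that serious events more than 30 days after the last dose are generally reported only if a link to the study drug is suspected.

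**The concern.** A *possibly related* level normally takes the events for which the drug is a credible cause but not the only one. Table 12 does not allow that: any other possible explanation rules the level out. It also rules out a reaction not already known for the drug.

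The protocol's own content makes these cases likely. Four drugs are given to patients with extensive-stage disease. Liver enzyme or bilirubin rises, diarrhea and neurotoxicity appear in both the camrelizumab table (Table 1) and the carboplatin table (Table 5). Hematologic toxicity appears for both apatinib (Table 3) and carboplatin (Table 4). Section 13.5 speaks of the test drug in the singular and does not say whether a partner study drug counts as another explanation.

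Bleeding is the clearest example. Section 1 reports vascular involvement in 42 of 50 cases in a retrospective series and says that it may raise the bleeding risk under anti-vascular therapy. Bleeding on apatinib is an anticipated reaction (Table 3), and the tumor is another possible explanation. That combination has no column in Table 12.

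At stake are the treatment-related rates, which are one of the two parts of the safety report, and the recording of some late events.

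**Working it through.** The plan states no figure on this point, so there is none to reproduce. The check treats Table 12 as a decision table.

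**Inputs (Table 12).**

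| Question | Definitely | Highly likely | Possibly related | Possibly unrelated | Unrelated |
|---|---|---|---|---|---|
| Plausible timing | √ | √ | √ | √ | × |
| Known reaction type | √ | √ | √ | × | × |
| Improves on removal | √ | √ | √ or × | √ or × | × |
| Recurs on re-administration | √ | ? | ? | ? | × |
| Another explanation | × | × | × | √ | √ |

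Two readings are assumed. The awkwardly worded second row is taken to mean a reaction type known for the drug. The question mark is taken first as any answer, then as unknown only.

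**Step 1: count the patterns.** Timing, known type, removal and other explanation each have 2 answers. Re-administration has 3 (yes, no, unknown). That gives 2 × 2 × 2 × 3 × 2 = 48 patterns, 24 of them with plausible timing.

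**Step 2: plausible timing, question mark as any answer.** Known type and other explanation form four combinations. Each has 2 × 3 = 6 patterns.

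| Known type | Another explanation | Result | Patterns |
|---|---|---|---|
| Yes | No | A related level | 6 of 6 |
| Yes | Yes | No column | 6 of 6 |
| No | No | No column | 6 of 6 |
| No | Yes | Possibly unrelated | 6 of 6 |

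**Step 3: implausible timing.** *Unrelated* needs ×, ×, ×, ×, √, which is 1 pattern. The other 24 − 1 = 23 fit no column.

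**Step 4: totals.** Related 6, possibly unrelated 6, unrelated 1, no column 6 + 6 + 23 = 35. The sum is 48. If the question mark means unknown only, 3 patterns are related and 42 fit no column.

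**Step 5: compare the related levels.** *Possibly related* differs from *highly likely related* only in the removal row. It is no more tolerant on known type or other explanation.

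**Step 6: effect on the reported rate.** For events with plausible timing, let A be the number of known type with no other explanation, B known type with another explanation, C new type with no other explanation, and D new type with another explanation. Table 12 labels A as related and D as not. It is silent on B and C, so the related count can lie anywhere from A to A + B + C, depending on how assessors fill the gap. The protocol gives none of A to D. At subject level, if all 36 planned subjects are in the safety set, each subject whose only related event falls in B or C moves the related-event incidence by 1/36 = 2.8 percentage points.

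**Step 7: collection.** Up to 30 days after the last dose and before any new anti-tumor treatment, events are recorded whatever their causality, so a missing category costs only the label. After new treatment starts, or for serious events beyond 30 days, the causality judgment decides whether the event is recorded or reported at all. Deaths within the serious-event reporting period are exempt from the first limit (section 13.6).

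**The case against.** The strongest objection is that the primary endpoint does not depend on Table 12. That stands. A reader might infer that new or competing-cause toxicities drop out of the primary safety result. They do not: events are defined and documented regardless of relation, and section 14.4 already tabulates them on an all-cause basis. Only the adverse-reaction part and the two causality-dependent collection rules are exposed.

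A reader might also infer that the table pushes such events into the unrelated levels. It does so only for a new-type event that also has another explanation. The other two problem combinations match nothing, and an assessor could file them either way. The unrelated columns need both features together, so neither feature alone leads there. A gap of this kind does not by itself fix the direction of bias.

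It can further be said that all four drugs are listed as study drugs, so an event explained by a partner drug could still be called drug-related. That is a reasonable reading. The singular wording in section 13.5 leaves it open, which is a reason to settle it in the text.

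Finally, the analysis is mainly descriptive, and no hypothesis or numerical stopping boundary uses a related-event rate. That limits the severity. It does not make the table usable as written.

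**Conclusion.** Table 12 is wrong as written in two respects. *Possibly related* excludes every event with another possible explanation or an unknown reaction type, and the five columns are not exhaustive. With plausible timing, two of the four combinations of known type and other explanation have no category. Overall 35 of 48 patterns have none, or 42 of 48 if the question mark means unknown only.

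The treatment-related rates in section 14.4 may therefore be understated, if assessors default unmatched events to not related, or may depend on the assessor. Some events after new anti-tumor treatment, and some serious events beyond 30 days, may go uncollected or unreported. All-cause tables within the collection window are not affected.

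The patterns counted are logical possibilities, not expected event frequencies. The protocol gives no adverse event rates, so the effect on any reported percentage cannot be computed. The conclusion rests on a literal reading of the table and on taking its second row to mean a reaction type known for the drug. This should be fixed, but it does not invalidate the primary endpoint.

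**What to change.** In Table 12:

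- Under *possibly related*, accept √ or × for another explanation when the reaction type is known.
- Under *possibly related*, accept an unknown reaction type when there is no other explanation.
- Keep *possibly unrelated* for an unknown type with another explanation.
- Let implausible timing alone give *unrelated*.
- State that the question mark means any answer, including not tested.

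With plausible timing this gives 6 + 6 + 6 = 18 patterns at a related level and 6 at *possibly unrelated*. The 24 with implausible timing are *unrelated*. The total is 48 and none is left over. Simply entering √ or × in both cells of *possibly related* would not work, because that level would then cover every *possibly unrelated* pattern.

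In section 13.5, state that a partner study drug does not count as another explanation when relation to study treatment is judged. In section 14.4, state that all-cause adverse events are the lead safety summary and that related events are shown second.

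The cost is a few table cells and two or three sentences. The downside is that more events will be labelled related, so the related-event rate will look less favourable and be less specific.
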